#### Statistical analysis

Statistical analysis will be carried out with IBM statistical package for the social sciences (SPSS) Statistics 27 and R environment. The same statistical pipeline will be run twice, in two sequential phases: (1) intention-to-treat analysis considering data from all randomized participants, including those that complete and drop out of the study (in case of missing values, an adequate method of imputation will be executed whenever appropriate, depending on the proportion of missing data and the missingness mechanisms); (2) per-protocol analysis including only those who have had a treatment adherence equal to or higher than 80%. The significant threshold will be set at a two-tailed *p*-value of 0.05, and an appropriate multiple comparisons correction method will be implemented.

Baseline demographic and clinical characteristics of participants in the different intervention groups will be described with central tendency, dispersion, and position measures and compared between the three groups using parametric or non-parametric tests. To address our primary hypotheses, we will use multiple regression models, which will include: (a) the difference between the follow-up and baseline values in the primary outcome measures as the explained variable; (b) the 3-arms intervention as the explaining variable, and (c) other confounding factors as covariates. We will consider sex, age, years of education, time since stroke, and the baseline score as fixed covariates. Moreover, we will contemplate the need to adjust for further unbalanced factors between groups that appear to correlate strongly with the outcomes. In case of violating the linear regression assumptions, transformations of the variables or methods of robust regression will be adopted. We will examine the secondary outcomes with the same pipeline in the per-protocol sample. Although the sample size was not calculated to allow interaction effects, we will examine potential mediator and moderator effects in this sample.

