**Results:**

The effects of the interventions on cognitive and emotional outcomes will be described in intention-to-treat and per-protocol analyses. We will also explore potential mediators and moderators, such as genetic, molecular, brain, demographic, and clinical factors in our per-protocol sample.

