### Assessments

Within two weeks before the interventions started and within two weeks after completing the interventions, we performed medical, cognitive, and physical assessments, neuroimaging, and biological samples collection. When possible, we evaluated patients who dropped out of the study in the follow-up assessment to comply with the intention-to-treat principle.

All the assessments were online except for brain scans, blood tests, and stool sample collection, which were done with extra safety measures at the Hospital Universitari Germans Trias i Pujol (Barcelona, Spain). We conducted online assessments through the Zoom platform (except for medical and physical visits, which were done using a hospital-specific platform). A few days before the assessment, we communicated to the participants the electronic platform which would be used, the link to access the virtual room, and any material they needed to have ready for the visit (e.g., printed documents or objects to do the physical tests).

The assessment timeline is presented in Table 2. Assessors received specific training and a written protocol of the assessment schedule and instructions. The same evaluators carried out the baseline and post-intervention measurements to minimize bias from inter-rater variability.

**TABLE 2 T2:** Assessments schedule.

	Enrollment and screening		Baseline assessments (within 2 weeks prior to the start of the intervention)					Intervention (12 weeks)	Post-intervention assessments (within 2 weeks after the end of the intervention)				
				
	Screening (telematic)	Visit 0 (telematic)	Visit 1 (telematic)	Visit 2 (telematic)	Visit 3 (telematic)	Visit 4 (in-person)	Visit 5 (in-person)		Visit 6 (telematic)	Visit 7 (telematic)	Visit 8 (in-person)	Visit 9 (in-person)	Visit 10 (telematic)
Information of study	✓	✓											
First review of criteria	✓												
Exhaustive review of criteria		✓											
Informed consent form		✓											
Medical story			✓										
General health status			✓							✓			
Neuropsychological tests				✓					✓				
Cognitive scales				✓					✓				
Psychological scales				✓					✓				
Anthropometric measures					✓					✓			
Physical fitness tests					✓					✓			
Lifestyle behaviors scales					✓					✓			
Blood extraction						✓					✓		
Stool sample collection						✓					✓		
Magnetic resonance imaging							✓					✓	
Intervention follow-up diary								✓					
Exercise bracelet								✓					
Qualitative interviews													✓

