## Discussion

The MindFit Project is a randomized controlled clinical trial that aims to assess the impact of mindfulness and PE combined with CCT on chronic stroke patients’ cognitive and emotional wellbeing. We predict that the three intervention groups will show improvements at the end of the trial, but we expect that these changes will be quantitatively and qualitatively different between groups. We expect that groups that have completed a combination of therapies will show more significant changes than those who have only done CCT. In addition, we hypothesize that there will be a different impact of mindfulness and PE on the cognitive and emotional domains.

Secondly, we plan to study the physiological mechanisms underlying the changes produced by mindfulness and PE through biomarkers to obtain evidence on the biological pathways affected by each intervention and the final effect on the structure and functioning of the brain. A final step in understanding the possible effects of our interventions will be to analyze which personal and clinical variables moderate their impact. In this regard, we will be able to determine which strategies are most suitable for each patient profile and thus lead stroke rehabilitation toward a personalized treatment model.

As a limitation of our study, we highlight the lack of a passive control group that prevents us from determining the efficacy of CCT alone. On the other hand, 3 months of intervention may not be enough to obtain robust and clinically meaningful results. There is a possibility that we will observe changes in biomarkers that are not reflected in behavior. Instead, there may be changes in cognition and emotional wellbeing that are not yet sufficiently established to see their molecular and brain correlates. Despite these limitations, the MindFit Project has the potential and ability to generate new knowledge at multiple levels of evidence, from molecular bases to behavioral changes associated with mindfulness and exercise therapies in chronic stroke patients. In addition, the integration of a qualitative perspective will help us understand the significance of these possible changes and their clinical relevance.

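### Secondary outcomes, mediators and moderators are analysed only in participants with at least 80% adherence, so these between-arm contrasts lose the protection of randomisation; the primary outcomes are not affected

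*Protocol article*

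**What the plan says.** Under Statistical analysis, the protocol article defines two analysis sets. The first is an "intention-to-treat analysis considering data from all randomized participants, including those that complete and drop out of the study". The second is a "per-protocol analysis including only those who have had a treatment adherence equal to or higher than 80" per cent.

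The same section then allocates outcomes to sets. For secondary outcomes: "We will examine the secondary outcomes with the same pipeline in the per-protocol sample". For mechanism and effect modification: "Although the sample size was not calculated to allow interaction effects, we will examine potential mediator and moderator effects in this sample". The Abstract (Results) agrees on the latter, placing mediators and moderators "such as genetic, molecular, brain, demographic, and clinical factors in our per-protocol sample", while it gives the cognitive and emotional outcomes both analyses.

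Three other places bear on the point:

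- Intervention adherence: adherence is a count of sessions performed. Instructors recorded attendance at guided sessions; participants recorded their independent sessions in a diary.
- Interventions: the combined programmes last about twice as long as the control programme. They include instructor-led groups, whereas control participants do every session alone.
- Assessments: "When possible, we evaluated patients who dropped out of the study in the follow-up assessment to comply with the intention-to-treat principle".

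The Discussion says of the moderator analysis that "we will be able to determine which strategies are most suitable for each patient profile".

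**The concern.** Adherence is observed after randomisation. Comparing arms only among people who reached 80% compares groups that randomisation did not form. If those who reach the threshold differ between arms in motivation, fatigue, support at home or anything else linked to change, the contrast mixes the treatment effect with who persevered. This covers quality of life, fatigue, sleep, fitness, MRI, blood markers and microbiome. Several proposed moderators (age, comorbidity, cognitive reserve, personality) are also plausible causes of adherence, so conditioning on it can distort the moderation being estimated.

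The choice also sits badly with the follow-up of dropouts. They were assessed where possible for the sake of intention-to-treat, yet the secondary data of those below 80% enter no stated analysis of those outcomes.

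A separate matter is the Discussion. It presents the moderator analysis as able to settle which strategy suits which patient, although the analysis section concedes that the trial was not sized for interactions.

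**Working it through.** **1. The plan's own figure.** Inputs from Power analysis: difference 0.75 SD, SD 1, two-sided alpha 0.05, power 0.80, three pairwise comparisons, 20% loss. With Bonferroni for three pairs (an assumption; it is the reading that fits):

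n = 2 × [(2.394 + 0.842)/0.75]² = 37.2 per arm; 37.2/0.8 = 46.5, so 47.

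Rounding up before inflating gives 38 and then 48. Unadjusted alpha gives 28 and then 35, and does not fit. The stated 47 per arm therefore reproduces, and there is no arithmetic error. The issue is the analysis set.

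**2. Bias from selecting on adherence, with no true treatment effect.** Let U be a standard normal tendency to adhere, with correlation ρ to the outcome after the planned covariates; outcome SD is taken as 1. If a fraction p of an arm adheres, the mean of U among adherers is φ(c)/p, where c is the point that U exceeds with probability p.

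- p = 0.80: 0.280/0.80 = 0.350
- p = 0.60: 0.386/0.60 = 0.644
- p = 0.85: 0.274; p = 0.50: 0.798

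The spurious difference is ρ times the gap between arms:

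| Adherent, arm A vs arm B (assumed) | Gap | ρ = 0.2 | ρ = 0.4 |
|---|---|---|---|
| 60% vs 80% | 0.294 | 0.06 SD | 0.12 SD |
| 50% vs 85% | 0.524 | 0.10 SD | 0.21 SD |
| equal rates, same selection | 0 | 0 | 0 |

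The arm with lower adherence is flattered when ρ is positive. Swapping the rates reverses the sign.

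A simulation agrees. At 60% vs 80%, ρ of 0.2, 0.3 and 0.5 gives a bias of 0.058, 0.088 and 0.147 SD, and a nominal 5% test rejects 5.6%, 6.4% and 9.1% of the time. At 60% vs 90% the bias is 0.09 to 0.22 SD and the rejection rate 6.6% to 15.2%. With equal adherence and the same selection, the rate stays at 5%.

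**3. Power in the smaller set.** For 0.75 SD at alpha 0.05/3, pairwise power is 0.89 with 47 per arm. It is 0.81, 0.74 or 0.66 if 80%, 70% or 60% of each arm adheres (about 38, 33 or 28 per arm).

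**4. Moderators.** For a binary moderator split 50/50, the interaction SE is twice the main-effect SE: 2 × √(2/n).

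- n = 47: SE 0.413; power for 0.75 SD = Φ(0.75/0.413 − 1.96) = 0.44; detectable at 80% power = 2.80 × 0.413 = 1.16 SD.
- n = 33: SE 0.492; power 0.33; detectable 1.38 SD.

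Both use alpha 0.05 without multiplicity correction. Even the full sample has under half the power for an interaction as large as the planned main effect.

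**The case against.** The strongest reply is that the primary objective is untouched: cognitive and emotional outcomes are analysed in all randomised participants first. That is right, and it limits the point to secondary and mechanistic aims.

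A reader might infer that randomisation is discarded or that baseline comparability is certainly lost. The article does not support that. Participants stay in their allocated arms, and the model adjusts for the baseline score, age, sex, schooling and time since stroke, with room for further unbalanced factors. What goes is the guarantee of comparability. The covariates remove only measured differences, so ρ above must be read as what remains after adjustment.

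A reader might also infer that the combined arms carry twice as many sessions to complete, so that fewer of their participants reach 80% and the bias favours them. The Interventions section says the duration is doubled, not the session count, and adherence is counted in sessions. Guided groups could equally raise adherence in the combined arms. Direction and size are therefore unknown.

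The statement that the pipeline is run twice might be taken to cover every outcome. The later sentence naming the per-protocol sample for secondary outcomes would then have no function, and the Abstract confirms the restriction for mediators and moderators.

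Asking how a mechanism works under adequate exposure is legitimate. That supports per-protocol mediation as a supplement, but not as the only analysis stated. Finally, low interaction power is openly conceded and would persist in the full sample, so it is no argument for changing the analysis set. It bears only on the Discussion sentence.

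**Conclusion.** The point holds for secondary outcomes, mediators and moderators, and does not reach the primary conclusion. The plan fixes a set selected on a post-randomisation, partly self-reported variable, and states no all-randomised analysis beside it. Because duration and delivery differ by arm, unequal selection is plausible, but it is not shown.

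The size rests on assumptions, since the article gives no adherence rates. With 80% vs 60% adherent and a residual correlation of 0.2 to 0.4, the spurious difference is 0.06 to 0.12 SD, in either direction; with equal selection it is zero. That is modest against the 0.75 SD target, but avoidable.

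The Discussion sentence on patient profiles claims more than the design can deliver: about 44% power for a 0.75 SD interaction with all 47 per arm, assuming a 50/50 moderator and uncorrected alpha. It is a statement of intent; no such conclusion has yet been drawn, and the Abstract already speaks of exploring.

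**What to change.** - In Statistical analysis, make the all-randomised, as-allocated analysis the main one for secondary outcomes and moderators. Use the imputation approach already planned, or all participants with available data for MRI, blood and stool measures.
- Keep the per-protocol set as a labelled sensitivity analysis. Per-protocol mediation may remain as a supplement.
- Align the Abstract with this.
- In the Discussion, replace the claim about patient profiles with a statement that moderator and mediator results are hypothesis-generating.

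Cost: wording and a further run of the existing models, with no new data collection. The missing-data work is real, because participants with MRI contraindications were not scanned and dropouts were assessed only where possible, so the assumptions must be stated. Estimates may also be somewhat diluted relative to full adherence.

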## Discussion

The MindFit Project is a randomized controlled clinical trial that aims to assess the impact of mindfulness and PE combined with CCT on chronic stroke patients’ cognitive and emotional wellbeing. We predict that the three intervention groups will show improvements at the end of the trial, but we expect that these changes will be quantitatively and qualitatively different between groups. We expect that groups that have completed a combination of therapies will show more significant changes than those who have only done CCT. In addition, we hypothesize that there will be a different impact of mindfulness and PE on the cognitive and emotional domains.

Secondly, we plan to study the physiological mechanisms underlying the changes produced by mindfulness and PE through biomarkers to obtain evidence on the biological pathways affected by each intervention and the final effect on the structure and functioning of the brain. A final step in understanding the possible effects of our interventions will be to analyze which personal and clinical variables moderate their impact. In this regard, we will be able to determine which strategies are most suitable for each patient profile and thus lead stroke rehabilitation toward a personalized treatment model.

As a limitation of our study, we highlight the lack of a passive control group that prevents us from determining the efficacy of CCT alone. On the other hand, 3 months of intervention may not be enough to obtain robust and clinically meaningful results. There is a possibility that we will observe changes in biomarkers that are not reflected in behavior. Instead, there may be changes in cognition and emotional wellbeing that are not yet sufficiently established to see their molecular and brain correlates. Despite these limitations, the MindFit Project has the potential and ability to generate new knowledge at multiple levels of evidence, from molecular bases to behavioral changes associated with mindfulness and exercise therapies in chronic stroke patients. In addition, the integration of a qualitative perspective will help us understand the significance of these possible changes and their clinical relevance.

## Dissemination

The results of the MindFit project will be presented in numerous peer-reviewed publications. We will also publish secondary analyses of the clinical trial, and cross-sectional studies will be developed with the participants’ baseline data. The results will also be presented at national and international conferences. Our research group will strive to publish the results regardless of their nature or direction concerning the initial hypotheses.

We will also promote the divulgation of the knowledge obtained: we will organize a closing day for our participants where we will present the main results; we will provide participants with published articles translated into Catalan and Spanish; we will create infographics with the results and publish them through our newsletter and social networks.

## Ethics statement

All participants gave written informed consent following the Declaration of Helsinki. The Bioethics Commission approved the protocol of the University of Barcelona (IRB00003099), the Germans Trias i Pujol University Hospital Research Ethics Committee (PI-17-110), the Healthcare Ethics Committee from the Institut Guttmann, and the Clinical Research Ethics Committee of IDIAP Jordi Gol (19/056-P).

## Abbreviations

APOE: apolipoprotein E
BDNF: brain-derived neurotrophic factor
CCT: computerized cognitive training
CRP: C-reactive protein
DNA: deoxyribonucleic acid
EDTA: ethylenediaminetetraacetic acid
ELISA: enzyme-linked immunosorbent assay
IGF-I: insulin-like growth factor I
IL-6: interleukin-6
MBSR: mindfulness-based stress reduction
MRI: magnetic resonance imaging
PE: physical exercise
SCFA: short-chain fatty acids
SPIRIT: standard protocol items: recommendations for interventional trials
SPSS: statistical package for the social sciences
TIDieR: template for intervention description and replication
VEGF: vascular endothelial growth factor.
